## Methods and design

### Ethics

Ethics approval was sought from the appropriate body in each country. The different regulations are described in an internal paper but one essential requirement in each country was that there should be special information sheets and consent forms for children. In order to fulfil this requirement, focus group work was undertaken in one of the centres, Northern Ireland, with parents and children to develop such materials.

### Population

The names of the children eligible for the study are recorded on CP registers covering all children in defined geographical areas, each child classified for impairment by type and extent. The registers share the same definition of CP [23], include all severities of CP and make every effort to be comprehensive by receiving notifications from multiple sources. Fourteen centres with such registers form a collaboration [23], and eight of these centres joined the present study (Table 1): North England, West Sweden, Northern Ireland, South East France, South West Ireland, East Denmark, Central Italy, South West France. A further centre in North West Germany joined the study after the start and followed all study protocols; however its sample could not be drawn from a validated population database and was constructed from referrals from clinicians, statutory and voluntary bodies working with children with cerebral palsy in a defined geographic area.

In order to maximise numbers in the smaller centres, children with dates of birth between 31/7/1991 and 01/04/97 inclusive (i.e. between 7 years 3 months and 12 years 11 months on 1^st ^July 2004) were included with the oldest being approached immediately and the youngest not until near their eighth birthday.

As milder cerebral palsy is more common, in the centres with sufficient numbers (1, 6) we sought similar numbers of children at each severity level by grouping children into four strata by walking ability and selecting a random sample from each stratum. Centres 2 and 3 selected a random sample of children in the stratum of best walking ability and approached all children in the remaining strata. In the smaller centres (4, 5, 7, 8) all children were approached.

The target sample size in each stratum of walking ability was estimated from power calculations using Life-H scores of children with CP [24]. A change of 2 in mean Life-H score allows the most participatory children with severe impairment to achieve what many children with only moderately severe impairment achieve. It was estimated that 30 cases were needed in each stratum to detect a difference in mean scores of 2 and that the European collaboration could provide such numbers.

### Training and visits

Training of the research associates from the different countries together was essential for quality control. They had to speak sufficient English to be able to take advantage of the training workshops, which included instruction in administering questionnaires, engaging children, disability issues and the rationale for the study. Following this, each research associate carried out up to five pilot visits in their own country; they all then met together again for the second training workshop at which difficulties and dilemmas were discussed and clear decisions made about how these should be resolved.

Children and families were therefore visited by researchers trained both to administer questionnaires to parents and to engage children for completion of their questionnaires. The visits usually took place in the child's home, lasting between 90 and 120 minutes. When the parents allowed it and the child agreed, the child completed the QoL instrument in private with the researcher.

Children with communication difficulties in addition to their CP were included by ensuring assistance from a parent, teacher or therapist as necessary. It was realised that some children with learning difficulties might not be able to report their QoL. A literature review was undertaken [25] to establish how to assess whether such children could self report their quality of life and how to interpret proxy responses from a parent or other person who knew the child well. The review showed that studies of assessment of QoL in children have never addressed the issue of self-report in children with intellectual impairment. Based on this review, we introduced a procedure to assess ability to respond to QoL questionnaires and in particular children's understanding and use of Likert scale The procedure, described by Cummins [26] for adults with intellectual impairment, was adapted for children [27]. The child is asked to order 3 real wooden cubes according to size; then to match each cube to a picture scale; then to mention things they dislike, like a bit and like a lot; then to match these to the picture scale. If successful the procedure is attempted with 5 levels.

### Instruments

The chosen instruments are listed in Table 2. An internal paper, available from the author, details how these instruments are scored and their psychometric properties.

QoL was captured by KIDSCREEN [28] which has been developed over the last four years by a multi-centre European research group. Its important features are that: it was developed from children's focus groups, it is designed for child or parent report, scaling has been developed using item response theory and shown to be consistent with a Rasch model, it possesses cross cultural validity in the translations already available and normative data are available from the general child population in each country.

Participation was captured by Life-H [24]. This instrument was developed in Quebec from a strong theoretical framework aligned with ICF [1], is well validated and has been used before in populations of children with CP.

Psychological and behavioural factors within the child were captured by the Strength and Difficulties Questionnaire SDQ [29]. This is also a well validated questionnaire and all necessary translations were already available. We used the parent report version.

Stress and functioning within the family were captured by the Parenting Stress Index [30], a well validated instrument. The Life Stress Scale of the index was used to measure the context of the parents' stress. Normative data were available from all countries in SPARCLE except Denmark – and a condition of permission to use the instrument was that normative data should be collected in Denmark following translation.

We also used the Child Health Questionnaire CHQ-PF50 [31]. This is a well validated questionnaire which has been used in many child studies, including some of children with CP. Normative data are available. It duplicates some data captured by other instruments in SPARCLE and is somewhat dated, being derived from adult questionnaires. However we decided to use it in case newer questionnaires did not function as expected and because it has a number of domains which could be used to assess construct validity of other instruments used in SPARCLE.

The numbers of children in the study, the defined impairments and socio-economic characteristics and the distribution of these factors are shown in Table 1.

To describe the environmental factors operating at a national or macro level, a review and search for relevant information was carried out by a social scientist. The results are available in an internal paper and include factors such as arrangements for educational provision, social attitudes, legislation on access to buildings, anti-discrimination legislation, transport design, rehabilitation, therapeutic services and assistive technology in the participating countries.

To describe the direct experience of environmental factors relevant to a particular child and family and the degree to which the environment helps or hinders, an instrument, the European Child Environment Questionnaire (ECEQ), was developed. Initial work included a literature review [32], and a qualitative study [33], followed by focus group work [34] in each country participating in SPARCLE. A domain structure was postulated on the basis of this qualitative work and is currently being verified using explanatory item response models [35].

As the Life-H instrument for participation does not capture frequency of participation for discretionary activities such as leisure, an instrument – the Frequency of Participation Questionnaire (FPQ) – was developed to capture frequency for those Life-H items for which it was meaningful. This was also administered to children in the general population in the relevant age range in each country to provide comparative normative data.

Translation of instruments followed international guidelines [36,37], with two forward translations and one backward one. A small amount of cultural adjustment was also needed concerning sporting activities, school types and parental socio-economic status. Table 2 details the translations undertaken.

### Data quality

To ensure data quality, questionnaires were photocopied and sent to the co-ordinating centre where data were entered into an Access database. This was a continuous process from which centres received immediate feedback about omissions, ambivalent entries or inconsistency in their returns so that corrections could be submitted. The database was programmed to assist accurate data entry, and further validations were performed after exporting into a statistical package (STATA 8). After 100 records, histograms of the distribution of responses for every question in every questionnaire were generated and inspected for face validity. Questionnaires from the first 500 children were double entered by an external company. As errors were less than 1% in all questionnaires except that about background factors, only this questionnaire was double entered for the remainder of the children.

### Statistical methods

Data quality will be assessed, in particular: heterogeneity between centres, the potential for bias due to non-response and the extent and pattern of missing data. We will compare the proportions of children in these categories in each centre with the overall proportion using a relative risk function [38]. We will assess whether non-response was related to age, gender and level of impairment and whether any such associations can explain the differences in response rates between centres [39].

The psychometric properties of the data captured by the instruments in Table 2 will be compared with the properties reported by their developers. The following will be undertaken where relevant:

• Cronbach alpha for internal consistency, within countries and overall;

• Convergent/divergent validity by considering correlations between domains and/or correlation with a similar instrument;

• Confirmatory analysis to evaluate whether the underlying factors in the data are consistent with those which have been reported in reference populations.

A separate paper will be submitted for publication around each instrument describing these validations, summarising the data, comparing with similar studies and using multivariate linear or logistic regression to assess how scores on each domain vary with level and type of impairment and socio-economic characteristics. Due to sampling within strata defined by walking ability by some centres, all analyses will be adjusted for gross motor function. A further paper will compare parents' and children's assessments of the child's quality of life and explore the factors influencing the differences; and another paper explores whether severity of impairment can be represented by a single or possibly two latent variables.

As North West Germany did not ascertain their cases from a population-based register, all analyses will include a sensitivity analysis with and without this centre.

We are also very interested in how the concepts captured by the instruments vary between countries. We are still not sure whether to compare countries using fixed effect or random effect (equivalent to multi-level) models to allow for any residual correlation of responses within centres that is not explained by the recorded variables [40]. We will then explore whether residual differences between countries can be explained by factors operating at national level, as determined by the work of the social scientist described earlier.

Following these initial assessments of how the data for each instrument relate to the child's impairment and the family's socio-demographic characteristics, relationships between the latent traits captured by the instruments will be analysed using structural equation modelling [41].

These models will address the principal hypotheses – that Environment affects QoL and Participation – in separate models for the various domains of the child's experience (e.g. physical, social and attitudinal environment at home and school). They will be built up iteratively, at first considering only Environment and QoL while stratifying by impairment, but subsequently introducing the direct and indirect influences of socio-economic factors, the child's personality and behaviour, and parental stress as possible modifying factors. Finally, we shall explore a model which includes both QoL and Participation.

Whilst many factors may influence both outcomes, our primary interest focuses on the effects of environment after allowing for other factors. By setting out in advance the relationships which may be causative, we expect that structural equation modelling will allow confirmation or rejection of those postulated causal links.

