**Methods/Design:**

A cross sectional study of children with cerebral palsy sampled from total population databases in 9 European regions. Children were visited by research associates in each country who had been trained together. The main instruments used were KIDSCREEN, Life-H, Strength and Difficulties Questionnaire, Parenting Stress Index. A measure of environment was developed within the study. All instruments were translated according to international guidelines. The potential for bias due to non response and missing data will be examined. After initial analysis using multivariate regression of how the data captured by each instrument relate to impairment and socio-economic characteristics, relationships between the latent traits captured by the instruments will then be analysed using structural equation modelling.

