### Overall purpose and hypothesis

Although a number of qualitative studies asking disabled children and their families to report their experience have yielded important insights into the lives and views of such children [4,5], larger populations of disabled children now need to be studied quantitatively to determine how and why participation and quality of life vary between children with comparable severity of impairment. We are studying children with cerebral palsy (CP) because:

• CP is the commonest cause of significant motor impairment, occurring in 1 in 500 births or 10,000 new cases a year in the EU prior to recent enlargement.

• Children with CP often have impairments of learning, hearing, vision, communication and epilepsy in addition to their motor ones and so are representative of the wider population of disabled children.

• Children with CP are a group with relatively stable impairment where Participation and QoL will be influenced by social and educational environmental factors as well as by medical interventions.

• Adults with CP are disadvantaged in social relationships and employment [17,18] and children are disadvantaged in education, social relationships and employment prospects [3,19].

• There are population registers of such children, reducing the risk of bias in selection of cases.

• Children aged 8–12 years were targeted because they are much less studied than preschool children, can self-report their QoL and have not entered the adolescent stage where additional factors operate.

The principal hypothesis addressed is that children with similar severity of impairment will experience variable outcomes, in terms of Participation and QoL, due to variation in Environmental Factors.

As some Environmental Factors will be consistent across a country but vary between countries, the study should allow the identification of those Environmental Factors which, if improved, will yield the greatest benefits for children and their families. Such knowledge will be invaluable in informing EU policy in the health, educational and social sectors.

Pre-specification of randomised controlled trials [20] and systematic reviews [21] increases confidence in conclusions reached but is not common practice in epidemiology. The aims of this paper are to specify objectives, hypotheses and methods prior to data analysis; and so increase confidence in the validity of the conclusions by avoiding the pitfalls of data dredging and *post hoc *analyses [22].

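### Structural equation models fitted to cross-sectional data cannot confirm or reject the causal links from Environment to QoL and Participation, as the protocol expects them to

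*Protocol article*

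**What the plan says.** The abstract describes the design as "A cross sectional study of children with cerebral palsy sampled from total population databases in 9 European regions". Families were visited to complete the questionnaires, and no follow-up measurement is described.

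The principal hypothesis (Overall purpose and hypothesis) is causal: children with similar impairment "will experience variable outcomes, in terms of Participation and QoL, due to variation in Environmental Factors". The intended use is causal too: "the study should allow the identification of those Environmental Factors which, if improved, will yield the greatest benefits for children and their families".

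Statistical methods then gives the analysis: "These models will address the principal hypotheses – that Environment affects QoL and Participation – in separate models for the various domains". On how the models are constructed it says: "They will be built up iteratively, at first considering only Environment and QoL while stratifying by impairment". Socio-economic factors, the child's personality and behaviour, and parental stress come in next, and a joint model of QoL and Participation is explored last. The section ends by saying that, because the possibly causative relationships are set out beforehand, "we expect that structural equation modelling will allow confirmation or rejection of those postulated causal links".

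Under Instruments, the ECEQ is described as recording a family's direct experience of the environment and "the degree to which the environment helps or hinders". National-level factors come from a separate review by a social scientist. The limitations paragraph of the Discussion covers development of the ECEQ and validity of the QoL instrument. It does not mention temporal order, reverse causation or unmeasured confounding.

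**The concern.** The closing sentence of Statistical methods gives the analysis a property that the design does not have. Fit to a covariance matrix observed at one time shows whether two constructs are associated after the modelled adjustments. It does not show which one drives the other, or whether something unmeasured drives both.

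The difficulty is concrete here. A rating of how far the environment helps or hinders a particular child can depend on how that child is faring, so a path from outcome to reported environment is a credible rival to the postulated one. Parental stress and child behaviour could be confounders, mediators or consequences, yet all enter as possible modifying factors. The meaning of the Environment path therefore changes as they are added.

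At stake is the reading of the principal result. If a clear path is taken as a confirmed causal link, it would be used to say which environmental changes would benefit children, in work meant to inform EU policy.

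**Working it through.** The plan gives no figure on this point. Its 30 cases per walking-ability stratum concern a difference in mean Life-H score and do not enter here. The check is algebra, followed by an illustration.

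**1. Reversal in the opening model.** Let E be Environment and Q be QoL, each with its own indicators.

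- Model E→Q: Var(E) = φ, Cov(E,Q) = βφ, Var(Q) = β²φ + ψ.
- Model Q→E: Var(Q) = φ′, Cov(E,Q) = γφ′, Var(E) = γ²φ′ + ψ′.

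Each model has three free structural parameters for three latent moments. Setting φ′ = β²φ + ψ, γ = βφ/φ′ and ψ′ = φ − γ²φ′ reproduces the first model's moments exactly. The measurement part is the same in both, so the implied covariance matrices are identical and the difference in fit is exactly 0 for any data and any sample size. Stratifying by impairment repeats this within each stratum.

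**2. Unmeasured common cause.** Suppose U, with variance 1, affects E by a and Q by b. The fitted E→Q path tends to β + ab/Var(E). With β = 0 it is still non-zero when ab ≠ 0. With β ≠ 0 and ab of opposite sign it can be close to zero. So neither confirmation nor rejection of a single causal link follows from the path.

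**3. Illustration.** All settings are assumptions, not figures from the protocol: n=800, three indicators per construct, one measured covariate S affecting both constructs, maximum likelihood, 12 degrees of freedom. One dataset was generated under each of three truths, and each was fitted with E→Q, with Q→E, and with no link.

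| Truth | χ² with E→Q | χ² with Q→E | χ² with no link | Fitted E→Q path |
|---|---|---|---|---|
| E causes Q | 18.39 | 18.39 | 113.04 | 0.41 |
| Q causes E | 14.24 | 14.24 | 97.67 | 0.40 |
| Unmeasured common cause only | 17.69 | 17.69 | 107.64 | 0.41 |

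Removing the link raises χ² by 94.65, 83.43 and 89.95 on one degree of freedom, so the path looks decisive every time. In the last two rows Environment has no effect on QoL.

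The fitted paths agree with what the generating values imply, conditional on S:

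- First row: the true effect is 0.40.
- Second row (effect of Q on E 0.4, residual SDs 0.9 for Q and 0.8 for E): 0.4 × 0.81 / (0.16 × 0.81 + 0.64) = 0.324/0.7696 = 0.42.
- Third row (U affects both by 0.6, residual SD 0.7): 0.36/(0.36 + 0.49) = 0.42.

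The figure of about 0.4 reflects the assumed inputs. The equality of the two fit columns does not.

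**4. Where each problem applies.** For the ECEQ, both reversal and confounding are open. For national-level factors such as legislation, one child's QoL cannot plausibly be the cause, so confounding is what remains.

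**The case against.** The strongest reply is that the plan makes its expectation depend on stating the links beforehand, names the order in which blocks enter, plans adjustment for several factors, and words the sentence as an expectation about postulated links. Structural equation modelling can also reject a pre-stated model whose restrictions the data contradict, and a fuller plan may hold path diagrams and retention rules.

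Part of this stands. Rejection of a whole over-identified model is possible, and the absence of diagrams or criteria from an article is not held against it. But stating the links in advance limits selective modelling; it supplies neither temporal order nor freedom from unmeasured confounding. Adjustment reaches measured factors only. No fuller plan could make one-time fit establish direction in the opening model.

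A reader might infer several stronger charges that the documents do not support:

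- *That staged model building contradicts the aim of avoiding data dredging.* The blocks are named in order beforehand, the joint model is presented as exploratory, and nothing says that paths will be added or dropped after inspecting fit.
- *That shared parental reporting manufactures the Environment–QoL association.* The Discussion says QoL is the child's own report wherever possible, with a proxy used only where the child cannot self-report. The size of any shared-report effect cannot be taken from the text.
- *That no later model can tell direction apart.* The exact equivalence is shown for the opening model, and in the illustration with one covariate affecting both constructs. For larger models it depends on path restrictions that are not shown.
- *That ECEQ scoring is tuned to the outcomes.* Scaling does take place within the study, but the domains were postulated from qualitative work, some independent validation data exist, and nothing links scoring to outcome data.

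**Conclusion.** The sentence is wrong as written and should be fixed. The analysis can show whether the data are consistent with the postulated links; it cannot confirm or reject them as causal. For direction in the opening Environment–QoL model, the result is exact and rests on no assumed figure: the two arrows fit identically. The illustrative path of about 0.4 under all three truths rests on the assumed settings and shows only that a strong, well-fitting path can arise with no effect of Environment.

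The point is confined to interpretation. It does not invalidate data collection or the planned estimates. It weighs most on the ECEQ-based environment, and for national-level factors it reduces to confounding. It still matters because it governs the conclusion drawn for the principal hypothesis and its policy use, and the limitations paragraph is silent on it.

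**What to change.** Replace the last sentence of Statistical methods with wording such as: *The models assess whether the data are consistent with the postulated links, assuming the stated direction and no unmeasured confounding; direction and causation cannot be established from cross-sectional data.*

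In addition:

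- List the cross-sectional design as a limitation in the Discussion, distinguishing the experienced environment (reversal and confounding) from national-level factors (confounding).
- State that equivalent reversed models exist and fit equally well. Running them beside the two-construct models is not needed, since identical fit cannot separate them.
- Label any path added or removed after inspecting the data as exploratory.

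The separate models by domain and the staged order can stay as planned. The cost is a few sentences and a weaker causal claim; no new data or change to the planned models is required.
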